### Active control group

Trained uro-physiotherapists will help the patients to initiate the PFMT program. At the beginning of the first session, the uro-physiotherapists will inform the patients of the history of PFMT and its benefits. Patients will be trained in a group of 6–8 patients. Before the training, clear goals for each session and the program as a whole will be given to all the patients. After each training session, the patient will fill out a treatment checklist and give suggestions related to the training. Uro-physiotherapists will then provide written/oral feedback for the patients on their improvement and concerns about their training. All the uro-physiotherapists will meet with the research team to ensure the consistency of the training protocol and discuss the concerns that may occur during the delivery of the training. The PFMT program meets the American College of Sports Medicine principles for prescribing exercise, including frequency, intensity, time, type, volume, and progression [20]. Patients in the active control group will receive PFMT twice per week for 5 weeks, making a total of 10 sessions. Every 2 sessions will be separated by at least 48 h. Each session lasts 50 min with a target of increasing pelvic floor muscle strength, power, endurance, and coordination in daily life context. The detailed training protocol will follow the Consensus on Exercise Reporting Template (CERT) [21]. It provides a direction for reporting exercise-related interventions regardless of exercise type and includes 16 items under 7 domains: what, who, how, where, when, dosage, tailoring, and compliance.

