### Group 1 (low-frequency electromagnetic stimulation)

Both electrical and magnetic stimulation are widely applied by the Department of Obstetrics and Gynecology as well as pelvic floor rehabilitation clinics for incontinence treatment. All the treatment will take place in a private environment. For the electrical stimulation section, patients will be asked to take off their pants and then lie on the treatment couch in the lithotomy position. After disinfection and the application of lubricating gel, a J-shape electrode will be placed into the vagina by an experienced uro-physiotherapist. The electrode is connected to a computer that controls the output of the current. Group 1 patients will receive the treatments with a frequency of 20–60 Hz and a pulse width of 200–600 μs. At the same time, to ensure that the patients do not suffer from any pain from electrical stimulation, the treatment amplitude will be adjusted according to the patient’s tolerance to the stimulation. After 10 min of electrical stimulation, patients will be asked to sit on a magnetic stimulation chair. A magnetic coil that can generate a magnetic field will be placed within the treatment chair’s seat. The magnetic coil will be controlled by an external power unit by the same therapist that delivers electrical stimulation therapy. The output of the magnetic stimulation consists of 15 Hz for 2 s and 30 Hz for 3 s, with a rest interval of 5 s, making up a total treatment period of 20 min. The treatment frequency will be two sessions per week for 5 weeks; a total of ten sessions will be initiated. Every two sessions will be separated by at least 48 h. After the electromagnetic stimulation, patients will complete a 20-min PFMT session, which will be the same as the active control group.

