### Group 2 (high-frequency electromagnetic stimulation)

Previous studies showed that low-frequency electromagnetic stimulation (twice or three times per week) has demonstrated efficacy in treating UI [22, 23]. However, one study showed that electrical stimulation was no more effective compared with sham treatment, which was controversial with other studies [24]. High-frequency electromagnetic stimulation refers to a regimen that uses a continuous daily treatment protocol, which has also demonstrated safety and efficacy in the treatment of UI [25, 26]. Another advantage of high-frequency electromagnetic stimulation is that patients can focus on the treatment and complete the entire course of treatment in a short period, with similar treatment effects compared with low-frequency electromagnetic stimulation. In the present study, we will adopt a 10-day, daily treatment regimen to match the total treatment volume with group 1. Each treatment session will be the same as group 1, to compare the effects of different treatment frequencies.

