#### Sample size {14}

The present study intends to apply ICIQ-SF as the primary outcome. After calculation, a sample size of 44 in each group is able to provide 80% power to detect a within-between-group difference measured using ICIQ-SF at three time points, assuming a small effect size (Cohen’s *f*) of 0.125 and a two-sided significance level of 5%. Considering that there is a 20% dropout rate, the study will increase the sample size to 165 in total.

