## Statistical methods

### Statistical methods for primary and secondary outcomes {20a}

The main analysis will follow the intent-to-treat principle with all the randomized patients included. The present study will keep the missing data and will not replace them. Normally distributed variables will be presented as mean (SD) values. Non-normally distributed continuous variables will be reported as medium values with interquartile ranges (25th–75th percentile), and percentages will be used for categorical variables. The Shapiro–Wilk test will be used to examine the normal distribution of the variables.

Baseline demographic data will be reported for all patients randomized to the three groups. These data include patients’ age, education level, employment, annual household income, and medical history (BMI, ever pregnant, cigarette smoking, and diabetes). Baseline data will be evaluated by *χ*
^2^ or Fisher’s exact for categorical variables, analysis of variance (ANOVA) for continuous variables, and the Kruskal–Wallis test for non-parametric variables.

Generalized estimation equation (GEE) models will be applied to analyze primary and secondary outcomes collected at different time points. Considering the potential effects of age, BMI, severity of UI, and other variables on the outcomes, subgroup analysis will be carried out to evaluate whether age (< / ≥  50 years), the severity of UI (ICIQ-SF < </ ≥  13 points), and BMI (< / ≥ 25 kg/m^2^) at baseline could have an impact on the effect of the treatment. In view of the fact that patients may not be able to complete all courses of the treatment due to various reasons during the treatment, we will also conduct per protocol analysis. Patients who have completed the original intervention as described above will be included.

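### Pelvic floor muscle training is given in groups of 6–8, but neither the sample size nor the described GEE provides for correlation within those groups

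*Protocol article*

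**What the plan says.** All from the protocol article.

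- **Active control group:** "Patients will be trained in a group of 6–8 patients", led by trained uro-physiotherapists, in 50-min sessions.
- **Group 1:** after stimulation, "patients will complete a 20-min PFMT session, which will be the same as the active control group". The same section says "All the treatment will take place in a private environment".
- **Group 2:** "Each treatment session will be the same as group 1, to compare the effects of different treatment frequencies".
- **Table 1:** the training in groups 1 and 2 is listed as the same as in control. The row for sustained contractions in the control arm describes patients completing the exercises by themselves.
- **Sample size {14}:** "a sample size of 44 in each group is able to provide 80% power", for a within-between difference over three time points, with a Cohen's f "of 0.125 and a two-sided significance level of 5" per cent. The only inflation is for 20% dropout, to 165 in total.
- **Statistical methods {20a}:** GEE "models will be applied to analyze primary and secondary outcomes collected at different time points". Section {20c} describes GEE in the same terms.

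No section mentions training group or therapist as a source of correlation, an ICC or a design effect.

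**The concern.** Patients are randomised one by one, but some or all of them are then treated together. Women in one training group share sessions and an instructor. The intervention description also adds strategies built on relatedness and interpersonal interaction. A positive correlation between their changes in ICIQ-SF is therefore plausible. It would arise after baseline, so it would not cancel from the change over time.

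A GEE that clusters on the patient handles correlation between one woman's repeated measurements. Its robust variance does not protect against correlation between different women. If the correlation is positive, confidence intervals for stimulation plus training versus training alone would be too narrow and type I error above 5%. That comparison is the trial's first aim. The 80% in the sample size section would then describe a trial with more independent information than this one has.

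**Working it through.** **Inputs from the article:** f = 0.125, k = 3 arms, m = 3 time points, two-sided 5% level, 44 per arm (N = 132), 20% dropout, 6–8 patients per training group.

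**Inputs assumed because the article does not give them:** within-patient correlation rho = 0.5, sphericity, 7 patients per group, ICC of 0.01, 0.05 and 0.10. The ICC refers to the change over time.

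**Step 1: reproduce the stated figure.** Repeated-measures within-between F test:

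- λ = f²·N·m/(1−rho) = 0.015625 × 132 × 3 / 0.5 = 12.375
- df1 = (3−1)(3−1) = 4; df2 = (132−3)(3−1) = 258
- power = 80.8%. With 43 per arm it is 79.7%, so 44 is the smallest balanced size that reaches 80%.
- 132/0.8 = 165.

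Both stated figures follow exactly with independent patients, so the calculation holds no allowance for training groups.

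**Step 2: variance inflation.** Design effect DE = 1 + (7−1)·ICC. If all arms are grouped, a pairwise difference has variance factor DE. If only control is grouped, the factor is (DE+1)/2.

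**Step 3: consequences.** Type I error of a patient-level pairwise test = 2·(1−Φ(1.96/√factor)). Power of a test with the correct variance uses λ/factor in the F test of Step 1.

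| | ICC 0.01 | ICC 0.05 | ICC 0.10 |
|---|---|---|---|
| DE | 1.06 | 1.30 | 1.60 |
| **Control only:** factor | 1.03 | 1.15 | 1.30 |
| SE ratio | 1.01 | 1.07 | 1.14 |
| type I error | 5.3% | 6.8% | 8.6% |
| power | 79% | 74% | 68% |
| **All arms:** factor | 1.06 | 1.30 | 1.60 |
| SE ratio | 1.03 | 1.14 | 1.26 |
| type I error | 5.7% | 8.6% | 12.1% |
| power | 78% | 68% | 58% |

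The control-only power applies the pairwise factor to the whole three-arm test and is approximate. None of the power figures includes the further small loss from having degrees of freedom based on the number of groups.

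**Step 4: simulation.** A naive three-arm interaction test, with 7 per group and the ICC taken as a share of the within-patient residual variance, gave these type I errors at ICC 0.01 / 0.05 / 0.10: 5.4% / 6.9% / 9.0% with control only grouped, and 6.3% / 11.6% / 20.5% with all arms grouped. Without clustering it was 4.7%. Under the alternative, the naive test still rejected about 80–83% of the time. Its apparent power survives because its error rate is no longer 5%.

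**Step 5: sensitivity.**

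- *Group size 6 to 8, all arms grouped:* power is 79% to 78%, 70% to 66% and 61% to 55% at the three ICCs.
- *5.6 completers per group (7 less 20% dropout), all arms grouped:* 79% / 71% / 62%.
- *rho = 0.6:* 89.5% without clustering. With all arms grouped, 79.0% at ICC 0.05.
- *rho = 0.7:* 82.6% with all arms grouped, even at ICC 0.10.
- *rho = 0.3:* 64.5% before any clustering.

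**The case against.** Five points on the other side deserve weight.

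1. **The article does not say that the GEE treats patients as independent.** It names no cluster level, working correlation or variance estimator, and an analysis plan that is not shown could add the training group. A reader might infer a stated independence assumption, but the text supports only that the one source of correlation mentioned is time. This objection does not reach the sample size, which is fixed in the article and reproduces without a design effect.
2. **The harm is conditional.** A reader might conclude that standard errors are too small and that 80% power will not be reached. Both need a positive ICC, and the article gives none. At 0.01 the loss is under 3 percentage points even with all arms grouped. True power also depends on an unstated rho: at 0.7 it stays above 80% with all arms grouped at ICC 0.10. A higher rho offsets the power loss but not the pairwise type I error inflation.
3. **Group format is explicit only for control.** Group 1 is treated in a private environment and has 20 min of training, against 50-min control sessions. The phrase "which will be the same as the active control group" may refer to exercise content alone. If so, the control-only figures apply, and the group 1 versus group 2 comparison has no training-group clustering.
4. **The mechanism should not be overstated.** Feedback concerns each patient's own improvement and concerns, and the article says that the motivational strategies have no direct effect on incontinence. It does not say that membership or the instructor stays fixed within a group. Shared sessions still make some correlation plausible.
5. **The remedy does not restore power.** To keep 80% with all arms grouped and rho = 0.5, 173 to 274 women would have to be randomised, depending on ICC (0.01–0.10) and group size (6–8). That is correct. The remedy makes inference valid and the stated power honest, and does no more.

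**Conclusion.** The point holds in conditional form. Training in groups of 6–8 is stated for the control arm and possible in the others. The sample size makes no allowance for correlation within training groups, and the GEE as described accounts only for repeated time points. If that correlation is positive, a patient-level analysis as written understates uncertainty for stimulation plus training versus training alone.

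The effect is minor at ICC 0.01. At ICC 0.05 it is material: pairwise type I error is 6.8% with control only grouped and 8.6% with all arms grouped, and power is 74% and 68%. These figures rest on assumed values of the ICC, rho = 0.5, sphericity and 7 per group. The article does not establish that true power is below 80% or that all arms are affected.

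**What to change.** 1. **Reconcile the delivery descriptions.** State which arms train in groups, so that the active control section, the group 1 and group 2 sections and Table 1 agree.
2. **Record a training-group identifier** for each patient, by session if membership can change. The article already plans a standardised record of each session, so this is one more variable. It may be hard to recover later.
3. **Account for it in the primary model.** Either use the training group as the independent cluster in the GEE, with a small-sample variance correction (for example Mancl–DeRouen) and degrees of freedom based on the number of groups, or use a mixed model with random effects for training group and patient. With 55 randomised per arm there are about 7 to 9 groups per arm (55/8 = 6.9; 55/6 = 9.2), so the small-sample correction matters. If only one arm is grouped, use a partially nested model with no group variance in the other arms.
4. **Amend Sample size {14}** to say that 80% power assumes no within-group correlation. State the rho used and give power over an ICC range such as 0.01–0.10.

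**Cost:** one extra variable, a changed model term and a less favourable stated power. Confidence intervals widen: at ICC 0.10 the standard error is about 14% larger if only control is grouped and 26% larger if all arms are. No extra patients are required, but power is then reported at its lower value and not restored.

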### Group 1 (low-frequency electromagnetic stimulation)

Both electrical and magnetic stimulation are widely applied by the Department of Obstetrics and Gynecology as well as pelvic floor rehabilitation clinics for incontinence treatment. All the treatment will take place in a private environment. For the electrical stimulation section, patients will be asked to take off their pants and then lie on the treatment couch in the lithotomy position. After disinfection and the application of lubricating gel, a J-shape electrode will be placed into the vagina by an experienced uro-physiotherapist. The electrode is connected to a computer that controls the output of the current. Group 1 patients will receive the treatments with a frequency of 20–60 Hz and a pulse width of 200–600 μs. At the same time, to ensure that the patients do not suffer from any pain from electrical stimulation, the treatment amplitude will be adjusted according to the patient’s tolerance to the stimulation. After 10 min of electrical stimulation, patients will be asked to sit on a magnetic stimulation chair. A magnetic coil that can generate a magnetic field will be placed within the treatment chair’s seat. The magnetic coil will be controlled by an external power unit by the same therapist that delivers electrical stimulation therapy. The output of the magnetic stimulation consists of 15 Hz for 2 s and 30 Hz for 3 s, with a rest interval of 5 s, making up a total treatment period of 20 min. The treatment frequency will be two sessions per week for 5 weeks; a total of ten sessions will be initiated. Every two sessions will be separated by at least 48 h. After the electromagnetic stimulation, patients will complete a 20-min PFMT session, which will be the same as the active control group.

### Group 2 (high-frequency electromagnetic stimulation)

Previous studies showed that low-frequency electromagnetic stimulation (twice or three times per week) has demonstrated efficacy in treating UI [22, 23]. However, one study showed that electrical stimulation was no more effective compared with sham treatment, which was controversial with other studies [24]. High-frequency electromagnetic stimulation refers to a regimen that uses a continuous daily treatment protocol, which has also demonstrated safety and efficacy in the treatment of UI [25, 26]. Another advantage of high-frequency electromagnetic stimulation is that patients can focus on the treatment and complete the entire course of treatment in a short period, with similar treatment effects compared with low-frequency electromagnetic stimulation. In the present study, we will adopt a 10-day, daily treatment regimen to match the total treatment volume with group 1. Each treatment session will be the same as group 1, to compare the effects of different treatment frequencies.

#### Criteria for discontinuing or modifying allocated interventions {11b}

Patients of the study are allowed to withdraw from the study at any time for any reason if they wish to do so without any consequences. The researchers of the study can also discontinue the participation if the participant is uncooperative and does not attend the study visits, and this patient will not be replaced by a new patient.

#### Strategies to improve adherence to interventions {11c}

To improve patient adherence, individuals who participate in the study will be closely supervised by interventionists with feedback for each treatment session. On an institutional level, all the interventionists and the researchers will have discussions on improving the delivery of the intervention and exchange their opinions on a weekly basis. Details of each intervention session will be recorded in a standardized document.

#### Relevant concomitant care permitted or prohibited during the trial {11d}

Participants who are taking medication for UI or have an impact on the skeletal muscle are prohibited from participating in the trial. Participants anticipated to wear a pacemaker due to a cardiac issue are also prohibited from enrollment. The research team will establish good palliative and emergency care management in case of any potential life-threatening issues.

#### Provisions for post-trial care {30}

The aim of the trial is to establish a comprehensive and standardized program for UI, and the participants will be able to continue beyond the trial. According to previous research, the trial does not include any specific risks, and there will be no provisions for compensation.

### Outcomes {12}

The primary outcome of the study is the International Consultation on Incontinence Questionnaire–Short Form (ICIQ-SF) [27]. It is a widely used four-item questionnaire with full validation that assesses the voiding frequency, voiding volume, impact on quality of life, and the cause of leakage during the past 4 weeks. The total score of the questionnaire ranges from 0 to 21, with 0–7 representing mild UI, 8–12 representing moderate UI, and 13–21 representing severe UI.

The secondary outcomes include (1) a 3-day bladder diary, which records the micturition frequency, incontinence episodes, fluid intake, times of voiding, voided volume, and pad usage per 24 h for 3 days. Previous observational studies have demonstrated the reliability and reproducibility of data from bladder diaries and standard symptom evaluation [28]. The duration of the diary between 3 and 7 days is usually reported in the literature, while the present study plans to apply the 3-day voiding diary due to the consideration of patients’ compliance and convenience. (2) Pelvic floor muscle function, which includes the modified Oxford Grading Scale, pelvic floor electromyography, and pressure measurements. With high inter- and intra-rater reliability [29, 30], the modified Oxford Grading Scale allows the quantification of pelvic floor muscle strength as 0, no contraction; 1, flicker; 2, weak; 3, moderate; 4, good; and 5, strong. The Glazer Protocol-embedded electromyography assesses the muscle activities during different stages such as baseline rest, phasic contraction, tonic contraction, endurance contraction, and post-contraction rest. The results of the test could reflect the supportive, sexual, and sphincter function of the pubococcygeus muscle [31]. Pressure measurement is another traditional way to assess pelvic floor muscle function, along with Oxford Grading Scale and electromyography; this multidimensional assessment model allows for a more comprehensive evaluation of pelvic muscle function. (3) Pelvic organ prolapse quantification (POP-Q) system, which is widely used in clinical settings and provides the characterization of a woman’s prolapse. The detailed technique of performing a POP-Q test has been described in the ICS/IUGA statements [2, 32]. (4) SF-12 Health Survey, which is one of the most widely used instruments that assess self-reported health-related quality of life. Compared to the original version SF-36 [33], the SF-12 covers all eight domains with fewer questions, which makes it more practical for patients to complete. Meanwhile, the Chinese version of SF-12 has been validated, which has similar psychometric properties as the English version [34].

#### Project timeline {13}

The timeline is presented in Table 2.

**Table 2 Tab2:**
[figure not shown]
The participant timeline

#### Sample size {14}

The present study intends to apply ICIQ-SF as the primary outcome. After calculation, a sample size of 44 in each group is able to provide 80% power to detect a within-between-group difference measured using ICIQ-SF at three time points, assuming a small effect size (Cohen’s *f*) of 0.125 and a two-sided significance level of 5%. Considering that there is a 20% dropout rate, the study will increase the sample size to 165 in total.

